### Assessment

This study will consist of two assessments: A and B (see Figure 1). Assessment A will take place at the same time as assessment 2 of the prospective study (6 months after the AMK investigation). Assessment B will take place six months later, at the same time as assessment 3 of the prospective study (12 months after the AMK investigation).

At assessments A and B, children and parents will be asked to complete a questionnaire. A member of the research team will meet the parent and child at a place of their choice (in most cases their own home) to assist them. The way in which the questionnaire is to be completed will be discussed with the parent and the child, and will depend on the participants’ reading and writing skills. If reading and writing skills are poor, a research team member will read out the questions and write down the participant’s answer on the questionnaire form. If reading and writing skills are sufficient, participants may choose to complete the questionnaire by themselves. To prevent the parents from influencing the children’s answers, parents and children will be requested to complete their questionnaires in separate rooms. Respondents will be rewarded for their participation by a 10 euro gift voucher for the parents, while the children will receive either a 5 euro gift voucher (children > 10) or an age-appropriate present (6–10 years).

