#### (1) Effectiveness study

A multivariate regression analysis will be performed in which outcomes of mental health and quality of life will be compared between the Child-Interview intervention group and the control group (adult-only intervention). This will be done at follow-up (assessment B), 6 months after assessment A and a year after the intervention. Covariates will be taken into account.

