#### (2) Economic evaluation study

In this study, additional costs and additional outcomes of the Child-Interview intervention will be compared with those of the adult-only intervention. The incremental cost-effectiveness ratio (ICER) will be expressed as the incremental costs per degree of improvement in mental health of the Child-Interview intervention group in comparison with the control group (adult-only intervention). The incremental cost-utility ratio (ICUR) will be expressed as the incremental costs per QALY of the Child-Interview intervention group in comparison with the control group (adult-only intervention).

The ICER (and ICUR) will be calculated using ICER = (Ci-Cc)/(Ei-Ec), where Ci is the annual total costs of the Child-Interview intervention, Cc the annual costs of the adults-only intervention, Ei the effect at 6-months follow-up for the Child-Interview intervention and Ec the effect at 6-months follow-up of the adult-only intervention. The robustness of the ICER will be checked by non-parametric bootstrapping (1000 times). The bootstrap replications will be used to calculate 95% confidence intervals around the costs. The bootstrapped ratios (ICER and ICUR) will be graphically presented in two ways: (1) plotted in a cost-effectiveness plane, in which the vertical line reflects the difference in costs and the horizontal line reflects the difference in effects, and (2) in a cost-effectiveness acceptability curve, showing the probability that the Child-Interview intervention is cost-effective based on a range of ceiling ratios (the maximum amount of money society is willing to pay to gain one extra unit of effect or a gain in QALY). Additionally, the robustness of the base-case findings will be assessed using a sensitivity analysis [42]. This economic evaluation will be performed from a societal perspective. Bootstrapping will be carried out in Excel.

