Another limitation is the possible recall bias caused by the time that elapses between the assessment moments. A period of 3 months is generally used between assessments in economic evaluations. However, this study will use a period of 6 months because the assessment moments will be connected to those of the ongoing prospective study. Respondents may have difficulty remembering the exact number of times they used healthcare and other services, which may affect outcomes.

To conclude, within the constraints of ethical and legal standards, the quasi-experimental study design we chose is expected to provide information on the optimal approach for AMK investigation, in terms of effectiveness and cost-effectiveness. The aim of an AMK investigation is to refer the child and family to well-tailored care and to end substantiated maltreatment. The use of the Child-Interview intervention may contribute to the prevention of negative outcomes of child maltreatment, if using this intervention during the AMK investigation proves to result in better mental health and quality of life outcomes for maltreated children because well-tailored care can be provided on the basis of information that cannot be retrieved with the adult-only intervention. Policy makers are increasingly interested in the cost-effectiveness of methods being used, and cost-effectiveness studies are increasingly used in the development of new policies.

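### The ICER and ICUR set annual costs against an effect at an unclear time point, and for the QALY the windows do not match on either reading

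*Protocol article*

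**What the plan says.** All references are to the protocol article.

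- **Formula** (Analyses, (2) Economic evaluation study): "The ICER (and ICUR) will be calculated using ICER = (Ci-Cc)/(Ei-Ec"). One formula serves both ratios.
- **Numerator** (same section): "Ci is the annual total costs of the Child-Interview intervention", with Cc likewise annual.
- **Denominator** (same section): Ei has the label shown in "Cc the annual costs of the adults-only intervention, Ei the effect at 6-months follow-up", and the control term matches it: "Ec the effect at 6-months follow-up of the adult-only intervention". The ICER is expressed per unit of improvement in mental health, the ICUR per QALY.
- **Timing** (Assessment): "Assessment A will take place at the same time as assessment 2 of the prospective study (6 months after the AMK investigation"), and "Assessment B will take place six months later, at the same time as assessment 3 of the prospective study (12 months after the AMK investigation").
- **Effectiveness analysis** (Analyses, (1) Effectiveness study): "This will be done at follow-up (assessment B), 6 months after assessment A and a year after the intervention".
- **QALYs** (Quality adjusted life years (QALYs)): the child rates health over the past 6 months from 1 to 10, and the score is divided by 10. The difference in this value from A to B is multiplied by how long the effect lasts. No length is given.
- **Spacing** (Discussion, on recall): "this study will use a period of 6 months because the assessment moments will be connected to those of the ongoing prospective study".

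**The concern.** A cost-effectiveness ratio needs costs and effects over the same stretch of time. Here the numerator is labelled as a year and the denominator as six months. The effectiveness analysis is placed at one year, so the effect in the ratio may not be the effect reported as the main clinical result.

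The QALY rule adds a separate problem. Both assessments come after the intervention, so assessment A is not a baseline. A change measured from A removes whatever benefit the child interview had already produced by month 6, while annual costs include those same six months.

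Cost-effectiveness is the study's second stated aim, and the results are meant to be plotted on a cost-effectiveness plane and read against ceiling ratios. An analyst following the text could choose either time point for the ICER. For the ICUR, the analyst would have to use a denominator that does not measure a year's health gain.

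**Working it through.** The plan gives no cost or effect figures, so there is none to reproduce. The check compares the definitions and then shows their consequences with assumed values.

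**1. What the six-month label can mean**

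| Reading | Origin of the 6 months | Assessment | Months since investigation | Same time as effectiveness analysis? |
|---|---|---|---|---|
| 1 | AMK investigation | A | 6 | No (that is at 12) |
| 2 | Assessment A | B | 12 | Yes |

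The Assessment section counts from the investigation, which favours reading 1. The Effectiveness section uses the word follow-up for B and places it six months after A, which favours reading 2. No sentence decides between them.

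**2. Mental-health ICER**

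Assume an annual cost difference of 1,000 euros and divide by the score difference at each time point.

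| Score difference at month 6 / month 12 | Annual cost ÷ month-6 effect | Annual cost ÷ month-12 effect |
|---|---|---|
| 1 / 1 | 1000/1 = 1,000 | 1000/1 = 1,000 |
| 1 / 2 | 1000/1 = 1,000 | 1000/2 = 500 |
| 2 / 1 | 1000/2 = 500 | 1000/1 = 1,000 |

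The ambiguity does no harm if the effect is stable. It moves the ratio in either direction if the effect grows or fades. Under reading 2 the score difference at B fits costs over months 0–12. If improvement were instead taken as each child's change from A to B, it would cover months 6–12 only.

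**3. ICUR**

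Let D_A and D_B be the between-group differences in utility at A and B, and T the unstated duration, taken as equal in both groups.

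- Stated rule: QALY difference = (D_B − D_A) × T.
- Accrual over the year: QALY difference = 0.5 × D_A + 0.5 × D_B. Each thermometer answer refers to the preceding six months, so A stands for months 0–6 and B for months 6–12.

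With assumed values:

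| Pattern | D_A | D_B | Stated rule | Accrued over months 0–12 |
|---|---|---|---|---|
| Constant gain | 0.05 | 0.05 | 0 × T = 0 | 0.025 + 0.025 = 0.050 |
| Gain fading by half | 0.05 | 0.025 | −0.025 × T | 0.025 + 0.0125 = 0.0375 |
| Gain only after A | 0 | 0.05 | 0.05 × T | 0 + 0.025 = 0.025 |

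With the same 1,000 euros, a constant gain gives 1000/0.050 = 20,000 euros per QALY by accrual. The stated rule divides by zero, so the ratio is undefined. With a fading gain the stated rule gives a QALY loss, although the intervention group is better off at both assessments. In the third row the stated rule equals accrual only if T = 0.5 year; with T = 1 it gives 0.05, twice the accrued value.

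**4. Does the reading of the label rescue the ICUR?**

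No. Under reading 1 the effect would be needed at A, but the QALY rule cannot be evaluated there because it requires B. Under reading 2 the rule can be evaluated, but it contrasts B with A and so does not represent the year over which costs are summed.

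**The case against.** The strongest reply is that the label is merely loose. The Effectiveness section calls B the follow-up and dates it six months after A, so the same words in the economic section may well mean B. For the mental-health ICER that is a fair reading, and with the score at B there is then no mismatch. A reader might infer from the formula that 12-month costs are certainly divided by a month-6 effect. The documents do not support that certainty; they support only an ambiguity that conflicts with the month-12 analysis if the months run from the investigation.

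It could also be said that change from A helps with groups that are not equivalent at the outset. But A is itself post-intervention, so subtracting it removes effect along with any prior imbalance. That imbalance is a matter for covariate adjustment, which the article already foresees for the effectiveness analysis.

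Two further inferences should not be drawn:

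- **That the ICUR is doubled.** This would follow if a constant gain were accrued for six months against annual costs. The stated rule does not accrue levels. It takes a change and multiplies it by an unspecified duration, so no fixed factor follows.
- **That the cost of the child interview falls outside the cost windows.** The adapted cost questionnaire lists the AMK among its services, its recall window is not stated, and Ci is described as total costs. Omission is not established.

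**Conclusion.** The point holds in two parts of different weight.

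- **ICER:** the effect time point is ambiguous. Read from the investigation, it contradicts the effectiveness analysis at month 12; read from A, it is consistent if the effect is the between-group score difference at B. This is a defect of wording, but one that can change the ratio if the effect is not stable between months 6 and 12.
- **ICUR:** the mismatch remains on either reading. The QALY rule discards benefit present at A while costs cover a full year, and its multiplier is undefined. With a constant advantage the QALY difference is zero whatever its size; with a fading advantage the sign reverses.

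The figures 0.05, its half and 1,000 euros are illustrative, since the article supplies none. The accrual formula assumes that each thermometer answer describes the six months before it, as the question is worded. The real size of the error depends on how any effect is spread over the year and cannot be computed from the document. The plan should be corrected before the economic analysis is run.

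**What to change.** Set one 12-month horizon, counted from the AMK investigation, in both the QALY section and the economic analysis section:

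1. **Costs:** Ci and Cc are the costs over months 0–12, obtained by adding the reports at A and at B. State the period that each report covers.
2. **ICER effect:** the between-group CBCL difference at assessment B, signed so that a lower problem score counts as improvement.
3. **QALYs:** accrue over months 0–12 as 0.5 × utility at A + 0.5 × utility at B for each child, in place of the A-to-B change times a duration.
4. **Wording:** replace the six-month label on Ei and Ec with assessment B (12 months after the investigation) for the ICER, and with QALYs over months 0–12 for the ICUR.

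No extra data collection is needed, because both cost reports, both thermometer scores and the CBCL at B are already planned. The cost is an edit to two sections and a small change to the QALY calculation, with the bootstrap run on the revised quantities.

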## Discussion

The value of having children participate in the AMK investigations by using the Child-Interview intervention is increasingly being recognized. The intervention yields valuable information to substantiate the alleged maltreatment report, and the intervention is also expected to be beneficial for the mental health and quality of life of the maltreated children. However, this beneficial effect has not yet been studied. In addition, child maltreatment is associated with substantial societal costs because of the high demand for healthcare and other services by both the maltreated children and their families. Using the Child-Interview intervention may prevent or reduce negative outcomes of child maltreatment, which may result in a lower consumption of healthcare and other services.

Although the AMK manual suggests that using the Child-Interview intervention during AMK investigation is the preferred method, the AMKs in the Netherlands are still in a transition period as regards the nature of the investigation. From a small survey among AMKs we estimate that the adult-only intervention is still used in approximately 40% of all investigations by the AMKs. At this point in time, this enables us to answer the research questions by means of the proposed quasi-experimental design, before the Child-Interview intervention is fully adopted, as the percentage of cases in which the intervention is not used is still sufficient. We will be able to derive two study groups with acceptable sample sizes from an ongoing study examining the mental health and quality of life of children reported as being maltreated.

A strong point of the proposed study is the use of child self-reports to collect data on quality of life, one of the main outcome measures of the effectiveness study. Data on quality of life are often collected using proxies, but research findings show discrepancies between child and proxy reports [43]. As a consequence, the value of obtaining children’s self-reports is increasingly recognized and several studies have established the accuracy and reliability of child reports [39,43-45].

Furthermore, not only will this be the first study to examine the effect of AMK involvement, it will also be the first economic evaluation performed in the Netherlands regarding an intervention for maltreated children. Since economic evaluations on child maltreatment have been scarce, it is expected that not all costs of healthcare and other services will be available yet. These costs will need to be valued for this study, so some of the costs will be based on estimates.

Additionally, many aspects of utility measurement in children have not yet been fully developed. There is a lack of health state classification instruments that consider children’s developmental stages, and there is a need to understand the role of proxies in assessing and valuing children’s health [46]. This is why we chose an alternative method, a visual analogue scale. The advantage of the thermometer method that will be used is that it is simple and therefore easily understood by children. However there are also disadvantages to this method, in that it generates values rather than utilities and does not involve an element of choice, nor decision-making under uncertainty, which may result in lower utility estimates.

A methodological concern for the quasi-experimental design of this study is the potential selection bias. All reports that are filed with the AMKs are discussed in a multidisciplinary team in which decisions about the best AMK investigation approach (Child-Interview intervention vs. adult-only intervention) are made. The choice of intervention is based on information collected from the reporter of the suspected child maltreatment. This reporter can be either a professional or non-professional (such as a neighbor), which may affect the quality and reliability of the information on which the multidisciplinary team must base their decision. In addition, AMK investigation using the Child-Interview intervention is the preferred method according to the manual for AMK investigations [13]. When the adult-only intervention is nevertheless chosen, there may be specific reasons for this, such as parents refusing their child’s participation in the AMK investigation, the child having been seen by a therapist or social worker, in which case this professional is approached to prevent additional strain upon the child, and/or language barriers. As a result of these limitations, the two groups may not be comparable at baseline, causing a concern regarding internal validity.

Another limitation is the possible recall bias caused by the time that elapses between the assessment moments. A period of 3 months is generally used between assessments in economic evaluations. However, this study will use a period of 6 months because the assessment moments will be connected to those of the ongoing prospective study. Respondents may have difficulty remembering the exact number of times they used healthcare and other services, which may affect outcomes.

To conclude, within the constraints of ethical and legal standards, the quasi-experimental study design we chose is expected to provide information on the optimal approach for AMK investigation, in terms of effectiveness and cost-effectiveness. The aim of an AMK investigation is to refer the child and family to well-tailored care and to end substantiated maltreatment. The use of the Child-Interview intervention may contribute to the prevention of negative outcomes of child maltreatment, if using this intervention during the AMK investigation proves to result in better mental health and quality of life outcomes for maltreated children because well-tailored care can be provided on the basis of information that cannot be retrieved with the adult-only intervention. Policy makers are increasingly interested in the cost-effectiveness of methods being used, and cost-effectiveness studies are increasingly used in the development of new policies.
